## **HANDLING OF UNEXPECTED OR ADVERSE EVENTS**

### **Response to new or unexpected findings**

All treatment failures will be treated with quinine as per the National Guidelines. If sufficient number of malaria cases are presenting to the clinic but enrolment is insufficient, the supervisor will need to determine at what point the problem with enrollment is occurring, and take steps needed to rectify the problem. If the problem is not remedied, the supervisor will report the poor enrollment to the investigators at CDC, Atlanta, and steps will be taken to either rectify the problem or to find a new site.

### **Identifying, managing and reporting adverse events**

We will be observing all the children for an hour following the ingestion of every dose of antimalarial. At every visit, patients will complete an adverse events history.

In the event of mild adverse reactions, it will be noted in the subjects case report form that these occurred; no further action will be taken by staff members, except in the case of vomiting, in which case the treatment medication may need to be re-administered. In the event of significant vomiting, the patient will be referred to the district hospital for further management. In the case of any severe adverse reaction (difficulty breathing, convulsions, and change in mental status) subjects will be referred to the district hospital for management. Transportation to the hospital will be provided.

Any adverse event which is severe, unexpected, and possibly related to the study, as well as any unanticipated problems involving risks to subjects or others and any occurrences of serious or continuing non-compliance will be reported to the CDC IRB according to CDC policy on incident reporting.

## EMERGENCY CARE

Any patient with treatment failure or recrudescence will receive quinine 10mg/kg/dose every 8 hours for 7 days. This will be given orally unless the patient has persistent vomiting, in which case the patient will be referred to the nearest hospital to receive IM/IV therapy.

Patients with signs of severe malaria (altered mental status, coma, convulsions, hemoglobin <5g/dl, respiratory distress, circulatory collapse, or abnormal bleeding), persistent vomiting or severe side effects will be hospitalized and receive parenteral therapy with artesunate (or quinine if not available) and relevant supportive treatments, according to National Guidelines.

Any participant who develops urticaria or difficulty breathing following administration of the treatment drug will be treated with diphenhydramine or chlorpheniramine and will be withdrawn from the study. In addition, patient and or their parents, caretakers and family members will be counseled that the patient should not receive additional doses of the antimalarial they were given. These patients will be treated with oral quinine for seven days as per the rescue protocol.

Adult patients and parents with children in the study will be encouraged to return to the clinic for any fever or other signs of illness on any day during the follow-up period, allowing for early detection and treatment of illness before it becomes severe. Any hospitalization which occurs during the follow-up period will be paid for by the study.

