## DATA HANDLING AND ANALYSIS

### **Data analysis plan, including statistical methodology and planned tables and figures**

SAS 9.3 (Cary, NC) as well as the WHO drug efficacy tools provided at <http://www.who.int/malaria/toolsformonitoring.html> will be used for data management and analysis. Data will be analyzed using two methods: **per protocol analysis**, where patients who were withdrawn from the study or who were lost to follow-up are excluded, and **survival analysis**, where all enrolled patients are included in the analysis until the last day before drop-out. In addition to voluntary withdrawals or treatment non-compliance, patients will be considered for the analysis as withdrawn if the PCR results are unclassifiable.

The final analysis will include:

- A description of the patients screened, and the distribution of the reasons for exclusion.
- A description of the patients included in the study.
- The proportion of patients lost to follow-up or withdrawn and the distribution of reasons for withdrawal.
- The proportion of treatment failures in each Pv arm at day 28 and day 42 with 95% confidence intervals using both methods of analysis.
- Frequency of side effects, severe malaria, anemia, and hospitalizations by treatment arm.
- Comparison in absolute means and relative changes in hemoglobin concentration during follow-up after treatment
- Comparison of number of recurrent parasitological vivax episodes after initial parasite episode.

**Data collection:** Data will be collected and recorded at the health facility by one of the trained staff members. All data entry forms will be checked for completeness. Laboratorians may complete brief reports on laboratory findings to share with clinicians who will transfer these results to the case report form of the appropriate patient, the laboratory results will be entered into an Excel database.

**Information management and analysis software:** Microsoft Excel (Redmond, Washington) will be used for double entry of laboratory data and clinical data. SAS 9.3 (Cary, NC) will be used for data analysis.

**Data entry, editing, handling, storage and disposition:** Some open-ended data including the names of specific drugs or diagnoses will be coded prior to data entry. A list of standard codes for these fields will be developed by hand once collection of data is complete. All forms will then be coded and checked by 2 different team members.

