## **METHODS TO MINIMIZE RISKS**

In order to minimize risks to patients, subjects will be followed closely for signs of recurrent parasitemia and hemolysis, with clinical and parasitological exams on days 1- 3, 7, 14, 21, 28, 35, 42, and monthly thereafter for one year. In addition, patients will be encouraged to return on any other day with signs of illness, fever, or dark urine. All patients will be observed closely for an hour following the first dose of medication. Any patient who develops urticaria or difficulty breathing following administration of the treatment drug will be treated with diphenhydramine or chlorpheniramine and will be withdrawn from the study. In addition, participants will be counseled that they should not take additional doses of other antimalarials (Annex IV).

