#### **ANNEX IV Drugs with antimalarial activity that should not be used during the study**

- chloroquine, amodiaquine;
- quinine, quinidine;
- mefloquine, halofantrine, lumefantrine;
- artemisinin and its derivatives (artemether, arteether, artesunate, dihydroartemisinin);
- proguanil, chlorproguanil, pyrimethamine;
- sulfadoxine, sulfalene, sulfamethoxazole, dapsone;
- primaquine;
- atovaquone;
- antibiotics: tetracycline\*, doxycycline, erythromycin, azithromycin, clindamycin, rifampicin, trimethoprim;
- pentamidine

\* Tetracycline eye ointments can be used.

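### For difficulty breathing after a study dose, the protocol gives conflicting instructions on hospital care and follow-on antimalarial and does not say which takes precedence

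*Protocol*

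**What the plan says.** Four places in the Protocol bear on a participant who has difficulty breathing after a study dose.

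- **Identifying, managing and reporting adverse events:** "In the case of any severe adverse reaction (difficulty breathing, convulsions, and change in mental status) subjects will be referred to the district hospital".
- **EMERGENCY CARE, second paragraph:** patients with signs of severe malaria, persistent vomiting or "severe side effects will be hospitalized and receive parenteral therapy with artesunate", with quinine as the fallback, in line with national guidelines.
- **EMERGENCY CARE, third paragraph:** "Any participant who develops urticaria or difficulty breathing following administration of the treatment drug will be treated with diphenhydramine or chlorpheniramine" and is withdrawn. The patient and family are told that "the patient should not receive additional doses of the antimalarial they were given". The paragraph closes: "These patients will be treated with oral quinine for seven days as per the rescue protocol". METHODS TO MINIMIZE RISKS repeats the antihistamine and the withdrawal but names no follow-on antimalarial.
- **END-POINTS, paragraph on valid end-points:** withdrawal is described as voluntary or involuntary, and patients who withdraw during days 0-2 receive chloroquine (CQ) under national policy.

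**The concern.** This is the instruction that clinic staff would turn to in an emergency. The protocol plans one or two staff for enrolment and clinical assessment, working in public health centres. Someone who opens one section finds a hospital referral. Someone who opens another finds an antihistamine, withdrawal and an oral course, with no mention of hospital. A third section supplies a different drug again for early withdrawals. Nothing says which text governs. What is at stake is the consistency and safety of care for an individual patient, not a statistical quantity.

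**Working it through.** No arithmetic applies: the protocol states no reaction rate and no figure rests on this rule. The check is to take one patient with difficulty breathing after a dose and read each instruction in turn.

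| Protocol section | Why the patient falls under it | Place of care | Follow-on antimalarial |
|---|---|---|---|
| Identifying, managing and reporting adverse events | symptom listed by name as a severe adverse reaction | referral to district hospital | not stated |
| EMERGENCY CARE, paragraph 2 | severe side effect; respiratory distress is also on its list of severe malaria signs | hospital admission | parenteral artesunate, or quinine if unavailable |
| EMERGENCY CARE, paragraph 3 | symptom listed by name | none mentioned | oral quinine, seven days |
| METHODS TO MINIMIZE RISKS | symptom listed by name | none mentioned | not stated |
| END-POINTS, valid end-points | withdrawn, if on days 0-2 | return to the clinic | CQ |

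**Step 1, place of care.** The adverse-event section and paragraph 2 point to the hospital. Paragraph 3 is silent. Referral and an antihistamine can be combined, so this alone is an omission rather than a contradiction.

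**Step 2, antimalarial.** Paragraph 2 gives parenteral treatment to an inpatient; paragraph 3 gives a week of oral quinine. The adverse-event section classes this symptom as severe, which brings the patient within paragraph 2. Paragraph 3 names the symptom, which brings the same patient within paragraph 3. The two drug instructions differ, and neither paragraph refers to the other.

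**Step 3, early withdrawal.** Paragraph 3 withdraws the patient. If the reaction falls on days 0-2, when AL or CQ is being given, the END-POINTS text calls for CQ where paragraph 3 calls for oral quinine. For a patient in the CQ or CQ+PQ arm, CQ is also the drug that paragraph 3 says must not be given again. Here the two texts cannot both be followed.

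**Step 4, which reactions are involved.** Convulsions and altered mental status are on the adverse-event list but not in paragraph 3, so the antihistamine and oral-quinine rule does not reach them. Urticaria alone appears only in paragraph 3 and METHODS TO MINIMIZE RISKS, so it has no place-of-care conflict. It does share the step 3 conflict on days 0-2.

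**The case against.** The best defence is that the texts divide the work. The adverse-event section says where the patient goes. Paragraph 3 is the specific rule for a reaction to a dose. Paragraph 2 is mainly a severe-malaria and persistent-vomiting rule, to which paragraph 3 is the exception. Paragraph 3 never says outpatient, and because it also covers urticaria it needs a path that does not require hospital. METHODS TO MINIMIZE RISKS is a short summary in the ethics part, and leaving quinine out there contradicts nothing. The CQ sentence could be meant for patients who choose to leave.

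Much of this is fair, and it reduces the place-of-care point to a missing cross-reference. It does not remove the drug conflict. The protocol does not say that paragraph 3 is an exception, paragraph 2 names severe side effects in their own right, and the END-POINTS paragraph counts involuntary withdrawal as withdrawal.

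A reader might infer three stronger points that the documents do not support.

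- **Reversed counselling.** METHODS TO MINIMIZE RISKS says "participants will be counseled that they should not take additional doses of other antimalarials (Annex IV"), and that annex includes "quinine, quinidine", the drug paragraph 3 gives. But the sentence moves from the reacting patient to participants in general and reads plausibly as the usual concomitant-drug warning. Annex IV also lists the components of the study drugs, so avoiding its contents includes avoiding the suspected drug. Read literally, it would forbid the trial's own treatments.
- **Bias in an outcome by arm.** The analysis plan lists "Frequency of side effects, severe malaria, anemia, and hospitalizations by treatment arm". The stated comparisons are AL against AL+PQ and CQ against CQ+PQ. Under Laboratory Evaluations each is made within one site, so a difference in practice between sites does not separate the arms compared. If the Intervention or treatment section is followed instead, AL versus CQ is itself randomised.
- **A count of patients affected.** Any such count needs a reaction rate that the protocol does not give. Referral is also not the same as admission.

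**Conclusion.** The protocol is wrong as written on one narrow point. A participant with difficulty breathing after a dose is subject to a hospital referral, to an inpatient parenteral regimen, and to a week of oral quinine with no hospital step. If withdrawn on days 0-2, CQ is added as a further alternative. That makes three follow-on antimalarial instructions with no stated precedence. For a CQ-arm patient on days 0-2, one of them contradicts the warning against repeating the suspected drug.

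The conclusion rests on two readings: that a symptom the adverse-event section calls severe is a severe side effect for EMERGENCY CARE, and that withdrawal for a reaction counts as withdrawal in END-POINTS. Both follow the natural sense of the text. The size is qualitative. No statement is made about how many patients would be affected, about distortion of hospitalisations by arm, or about which clinical rule is right.

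**What to change.** Reconcile the adverse-event section, the second and third paragraphs of EMERGENCY CARE, METHODS TO MINIMIZE RISKS and the withdrawal sentence in END-POINTS into a single reaction rule, with its content decided by the trial's clinicians. The rule should state which reactions are referred and which antimalarial instruction applies after withdrawal for a reaction, including on days 0-2. The other sections should refer to it rather than restate it. In METHODS TO MINIMIZE RISKS, separate the general warning about Annex IV drugs from the counselling given after a reaction, so that neither is mistaken for the other.

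The cost is wording in these sections. No patients, visits, procedures or form items are added.

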## ETHICAL ISSUES

### Consent Process

Staff members will fully explain the assessments to the participants and or their caretakers and ask for their consent/assent to participate. The written consent documents in English are attached as Annex VII. These will be translated in Afaan Oromoo and Amharic and then back translated to verify accuracy. These will be read to participants and or their caretakers in their respective local language. If a participant or parent/ guardian are illiterate, the consent form will be read to them in their respective local language and a thumbprint will be accepted as a legally effective signature. Consenting participants and or their caretakers will be advised that they are free to decline any question or procedure and that they may terminate their participation at any time without loss of any benefits.

**Purpose:** The clinical efficacy of the first-line antimalarials CQ and AL will be assessed using a WHO standardized procedure. The addition of PQ to CQ or AL, the WHO recommended regimen, will also be assessed. These results will be used to assist Ethiopia in re-assessing their national malaria drug policies and investigating therapeutic options for the future.

**Procedures:** During the course of the study, patients will receive an antimalarial and will undergo ~20 finger pricks to allow monitoring of parasitemia and anemia. Clinical assessments will be made on days 0, 1- 3, 7, 14, 21, 28, 35, 42, and then monthly for 1 year.

**Duration of participant involvement:** Patients will be involved in the study from day of enrollment (Day 0) until their 1 year follow-up.

**Experimental products or procedures:** No experimental therapies, products, or procedures will be used in this study. The use of AL for the treatment for Pv is common practice and WHO recommended practice in countries that have adopted AL for first-line treatment of Pf. Primaquine

is a standard component of therapy for Pv malaria illness to prevent relapses. The addition of PQ to a blood schizonticide (CQ or AL) is the WHO recommended regimen for Pv.

## **RISKS**

There is minimal physical and psychological risk associated with this study. The patient may experience a brief moment of physical discomfort and/or fear during the finger prick.

There is minimal risk associated with taking AL, CQ, or PQ. All of the drugs are recommended therapies in Ethiopia, have been widely used, and have been found to be safe (excluding those with G6PD deficiency for PQ). Studies of all of these combinations have reported only mild or moderate adverse events, including dizziness, headache, anorexia, nausea and abdominal pain, noting that these events may also be attributable to malaria. The use of PQ in those without G6PD deficiency is well-tolerated with mild GI discomfort when taken on an empty stomach. The protocol screens for G6PD deficiency, identifying those at hemolytic risk from primaquine therapy, and ensures those that are deficient are not given primaquine.

There are no social risks associated with this protocol. Malaria is a widely recognized disease in Ethiopia, and seeking treatment is socially acceptable. There are no economic risks associated with this study. Patients will be assessed and treated free of charge, and families will be given a stipend of 35 Ethiopian Birr (50Birr for those accompanied by a parent) per visit to cover their travel expenses. Any hospitalization that results from this study or during the follow-up period will be paid for.

## **METHODS TO MINIMIZE RISKS**

In order to minimize risks to patients, subjects will be followed closely for signs of recurrent parasitemia and hemolysis, with clinical and parasitological exams on days 1- 3, 7, 14, 21, 28, 35, 42, and monthly thereafter for one year. In addition, patients will be encouraged to return on any other day with signs of illness, fever, or dark urine. All patients will be observed closely for an hour following the first dose of medication. Any patient who develops urticaria or difficulty breathing following administration of the treatment drug will be treated with diphenhydramine or chlorpheniramine and will be withdrawn from the study. In addition, participants will be counseled that they should not take additional doses of other antimalarials (Annex IV).

## **ANTICIPATED BENEFITS**

This study is of direct benefit to participants. All patients will be treated for their initial parasitemia and followed to confirm parasite clearance. Any patient failing treatment with the treatment drug regimen will be treated with quinine, another standard antimalarial medication. At each visit, the patient, parent or guardian will be informed as to the status of their or their child's health, and the procedures and/or treatments that will occur during that visit and have the right to refuse a procedure or treatment or request transfer to the regular clinic and withdrawal from the study. Patients with malaria at government clinics receive for free whatever treatment is available in stock at the clinic. Although AL and CQ is the national policy, it is not always available in government clinics. Those patients assigned to the PQ arm will be given anti-relapse therapy which is currently not commonly practiced in Ethiopia.

The findings from the study will assist decision making to improve prevention and treatment of malaria in Ethiopia. With universal access to AL in Ethiopia since 2004 and the long-term use of chloroquine for Pv, monitoring for resistance to both these first-line drugs will be paramount. As a country pursuing elimination, effective treatment of Pv with PQ to prevent frequent relapses will provide both hematologic benefit for patients and decreased transmission in the community.

## **RISK/BENEFIT RATIO**

This study has minimal risks and significant benefit to the enrolled subjects.

## **VULNERABLE POPULATIONS**

**Children-** This minimal risk study includes children. Because this group has minimal natural immunity, this is the group most at risk for severe malaria, so any treatment must be efficacious in this age group. Adequate provisions are made for soliciting the permission of a parent or guardian.

**Non-English speaking participants-** It is imperative to carry out this study in the areas in which malaria is endemic; therefore, it is unavoidable that most participants will be non-English speaking. All consent forms have been translated into Afaan Oromoo and Amharic and back translated into English for accuracy; all explanations of the study procedures and clinical findings will be carried out in the patient's local language by local staff member.

## **INFORMED CONSENT/ PARENTAL PERMISSION PROCESS/ DOCUMENTATION OF INFORMED CONSENT**

Permission will be obtained from parent/ guardian bringing the child or the adult him/herself. Consent, and assent for children 7-17 years of age, will be appropriately documented prior to each patient's enrollment. As this study is minimal risk, permission from only one parent will be required. A staff member will read the form to the patient and or parent and give them a chance to ask questions. Patients and/or parents who are able to sign their name will be asked to sign the consent form. For non-literate persons, a thumbprint will be obtained in lieu of a signature. Children age 7-17 years of age will have a simplified assent form read to them. Details about the study and its benefits and potential risk will be explained to the patients in the language in which they are most fluent. All information regarding the patients will remain confidential to the extent legally possible. Unique numerical identifiers will be used for data entry.

## **JUSTIFICATION FOR WAIVER/ ALTERATION OF INFORMED CONSENT**

No justification for waiver or alteration of informed consent is being sought.

There is a large illiterate population in Ethiopia; thus there is a high likelihood that parents may be unable to sign their names. In this case, permission will be documented with a thumbprint as a legally effective signature in Ethiopia, following thorough explanation of the study and its benefits and potential risk to the patients and or parents/guardians in the language in which they are most fluent. A witness who is not involved with enrolling the patients and literate will witness and sign the informed consent.

## **ASSENT IMPLEMENTATION PROCESS/ DOCUMENTATION OF ASSENT**

Assent for children age 7-17 years of age will be sought.

